### Outcome measures

The data will be collected by research nurses at seven time points: before starting the first line palliative chemotherapy (T1; baseline), on the first day of each chemotherapy from cycle 2 to 4 (T2 to T4), at 3 months (T5), 6 months (T6), and 12 months (T7) from baseline. Figure 3 outlines the data collection for the current study. Primary outcomes are symptom, coping and quality of life at 3 months. Secondary outcomes are symptom, coping, and quality of life at 6 months, depression and self-efficacy for coping with cancer at 3 and 6 months, symptom and depression change from baseline to 3 months, and survival at 6 and 12 months among patients, and depression among caregivers at 3 and 6 months.

**Fig. 3 Fig3:**
[figure not shown]
Schedule of enrollment, interventions, and assessments

Edmonton Symptom Assessment Scale (ESAS) [44] + 4 core symptoms recommended to be evaluated in clinical trials (constipation, diarrhea, peripheral neuropathy) [45] as well as vomiting (expert opinion) (a total of 15 items (14 symptoms and 1 well-being item)) will measure symptom. Hospital Anxiety and Depression Scale (HADS) [46] will be used to measure depression of patients and family caregivers. Self-efficacy for coping with cancer will be evaluated using the Cancer Behavior Inventory (CBI) 3.0 Korean version [47]. Brief COPE [48] and EORTC QLQ C-30 [49] will be used to evaluate coping and QoL of patients. Data will be collected at baseline (before the start of first-line palliative chemotherapy), at 3 months, at 6 months, and at 12 months. Symptoms and depression during chemotherapy cycles (1^st^ to 4^th^ CTx) will be monitored (Fig. 3).

### Endpoints

The primary endpoints are symptoms, coping, and QoL at 3 months. Secondary endpoints are symptoms, coping, and QoL at 6 months, depression and self-efficacy for coping with cancer at 3 and 6 months, symptom and depression change from baseline to 3 months, survival at 6 and 12 months among patients, and depression among caregivers at 3 and 6 months. Any withdrawal from adverse events related to the intervention will be recorded and reported.

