### Randomization and blinding

The random allocation sequence was developed by the principal investigator (PI) before initiating patient enrollment. Research nurses will enroll and allocate patients according to the predefined sequence. Stratified permuted block randomization will be used to assign participants in a 1:1 ratio to the intervention or control group. Strata include the type of cancer (lung, breast, colorectal, gastric, liver/biliary/pancreas, or other cancers), age and sex of cancer patients. The minimization method will be applied after enrolling 60% of the participants in each cancer group to balance group allocation. Blinding is not considered applicable based on the type of intervention provided.

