### Intervention

The intervention will be “Enhanced Supportive Care”, consisting of 1) symptom management (symptom monitoring and management) and 2) coping enhancement counseling. The “Enhanced Supportive Care” sessions will be provided by nurses five times over three months. Administration of the sessions will take approximately 50 min per visit: 1) symptom management (20 min) + 2) coping enhancement counseling (30 min).

Fidelity of the intervention: Web-based symptom assessment and education application, symptom management education booklet for home use, and coping enhancement counseling protocols will strengthen the fidelity of the intervention.

Interventionist training and tracking: Before starting the intervention, a symptom expert (PI) will train research nurses in how to monitor symptoms and provide evidence-based symptom management education. A certified clinical psychologist will teach the principals of counseling and the third-wave psychotherapy Acceptance and Commitment Therapy (ACT) and train research nurses in coping enhancement counseling. Periodic retraining sessions will be held with a certified clinical psychologist.

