### Web-based symptom management system

The “Cancer Symptom Management System” application for the iPad [42] was upgraded to a web-based application to improve access from multiple digital devices. The upgraded web-based "Cancer Symptom Management System" application was developed using Python 3.7 and the Django framework. Every chart was rendered using Chart.js (https://www.chartjs.org), a popular open-source JavaScript library for visualizing data. The Cancer Symptom Management system was designed so that users (researchers) had to log into access data. Patients’ symptoms will be monitored using the “Cancer Symptom Management System” on an iPad. The results from symptom monitoring will be presented as a colored bar graph to the patients’ oncologists. Anxiety and depression scores will be generated and presented along with the symptom bar graph (Fig. 2). The generated symptom bar graph and the anxiety and depression scores will be uploaded to the patients’ Electronic Medical Records (EMRs) for oncologists’ review. Symptom management education will be provided by research nurses based on the results of symptom monitoring reflecting patients’ needs, as per a previous study [42].

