### Study procedures

The intervention group will receive the “Enhanced Supportive Care” consisting of 1) symptom management web-based symptom management system using iPad at each clinic visit (20 min) and 2) coping enhancement counseling (30 min). The “Enhanced Supportive Care” will be provided by trained nurses for 5 times over 3 months. Control group participants will monitor symptoms using web-based symptom management system using iPad at each clinic visits for 5 times and their symptom report will be delivered to oncologist via EMR, whereas neither evidence based symptom management education (using iPad and booklet) nor coping enhancement counseling by research nurses will be provided.

Participants could withdraw from the study upon request, and those who transfer to different hospitals, whose condition is deteriorated for study participation will be withdrawn from the study. Upon patients’ withdrawal, caregiver will withdraw as well.

Double data entry will ensure the integrity of the data. Collected information will be coded and stored for security, and the data will be monitored every 6 months.

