### Statistical analyses

Per-protocol analysis will be conducted for primary endpoints using data from completers at 3 months. Intention-to-treat analysis will be conducted using the imputed full analysis set as sensitivity analysis. Missing data from those who provided data other than baseline will be imputed using the last observation carried forward (LOCF) method for symptom and depression scores. SPSS Statistics (version 26, IBM Corp., Armonk, NY, USA), SAS (version 9.4, SAS Inc., Cary, NC, USA), R (version 4.0.2, Institute for Statistics and Mathematics, Vienna, Austria, www.R-project.org), and Mplus (version 8.4, MPLUS, Los Angeles, CA, USA) software will be used for data analysis.

Primary hypothesis: Advanced cancer patients who receive “Enhanced Supportive Care” (symptom management + coping enhancement counseling) will demonstrate fewer symptoms and better coping and QoL at 3 months (T5) compared to the control group of advanced cancer patients who receive usual care with symptom monitoring only.

Secondary hypothesis: Advanced cancer patients who receive “Enhanced Supportive Care” (symptom management + coping enhancement counseling) will demonstrate fewer symptoms and better coping and QoL at 6 months (T6), less depression, higher self-efficacy for coping with cancer at 3 months (T5) and 6 months (T6). Changes in symptoms and depression from baseline (T1) to 3 months (T5) will be different between the intervention and control groups. The intervention group will demonstrate longer survival at 6 months (T6) and 12 months (T7) than control group. Family caregivers of advanced cancer patients who receive “Enhanced Supportive Care” will demonstrate less depression than family caregivers of patients who were assigned to the control group at 3 months (T5) and 6 months (T6).

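### The one adverse-event rule the article states is limited to withdrawals judged related to the intervention, so its count cannot be compared between arms

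*Protocol article*

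**What the plan says.** All references are to the Protocol article.

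- **Endpoints** closes with the harm rule: "Any withdrawal from adverse events related to the intervention will be recorded and reported". No other sentence in the article mentions adverse events.
- **Intervention** defines the term that the rule depends on: "The intervention will be “Enhanced Supportive Care”, consisting of 1) symptom management (symptom monitoring and management) and 2) coping enhancement counseling".
- **Study procedures** describes the control arm: "Control group participants will monitor symptoms using web-based symptom management system using iPad at each clinic visits for 5 times". The same sentence withholds the education and the counselling from controls.
- **Study procedures** also gives withdrawal grounds that apply to everyone. One is the participant's own request; for the others, "those who transfer to different hospitals, whose condition is deteriorated for study participation will be withdrawn from the study".
- **Randomization and blinding**: "Blinding is not considered applicable based on the type of intervention provided".
- **Web-based symptom management system**: "Anxiety and depression scores will be generated and presented along with the symptom bar graph". Outcome measures and Endpoints then name depression as an outcome, but not anxiety.

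**The concern.** An event passes into the reported count only if someone judges it related to the intervention and it also leads to withdrawal. The first condition ties the count to a treatment that one arm does not receive, and leaves the judgement to people who know the allocation. The second excludes a patient who becomes more distressed during emotion-focused counselling but carries on.

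These patients have advanced cancer and are on first-line chemotherapy, so worsening is easily put down to disease or treatment. A report of no intervention-related withdrawals could then be read as evidence of safety, although the rule had little chance of showing anything else. Background withdrawals called related would err the other way, with no control rate to correct for them.

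**Working it through.** The plan states no harm figure, so there is none to reproduce. The check is mainly a reading of the sections against each other, followed by an illustration on assumed rates.

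**1. Who can enter the count.** Endpoints requires relatedness to the intervention. Intervention defines that as symptom management plus counselling. Under Study procedures, controls share only the symptom-monitoring component. A control withdrawal could arguably qualify if monitoring itself caused it, so the control count is near zero but is not fixed at zero.

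**2. Who judges.** The trial is open. Relatedness is therefore decided with allocation known, and in practice for one arm only.

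**3. What else captures harm.**

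| Possible harm | Stated by-arm comparison? |
|---|---|
| Death | Yes: survival at 6 and 12 months, log-rank test |
| Worse symptoms | Yes: 3 and 6 months, and change to 3 months |
| Worse quality of life | Yes: 3 and 6 months |
| Worse depression | Yes: 3 and 6 months, and change to 3 months |
| Worse anxiety | No: scored, but not an endpoint |
| Withdrawal, by reason | No: only related adverse-event withdrawals are named |

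The last two rows are the gap. Withdrawal reasons also matter because, under Statistical analyses, the primary analysis is per-protocol in 3-month completers. A patient who leaves because of worsening is outside it.

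**4. Illustration.** Inputs: 360 patients allocated 1:1 (Sample size determination; Design), so 360 / 2 = 180 per arm. The withdrawal rates below are assumptions, because the article gives none. The reported intervention count runs from none to all of the true events, depending on how many are called related. The control count is taken as about zero.

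| Assumed true rate, intervention / control | True counts | True difference (points) | Reported difference possible under the rule (points) |
|---|---|---|---|
| 5% / 2% | 180 × 0.05 = 9; 180 × 0.02 = 3.6 | +3 | 0 to +5 |
| 5% / 5% | 9; 9 | 0 | 0 to +5 |
| 2% / 5% | 3.6; 9 | −3 | 0 to +2 |

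Three different truths, including opposite signs, give overlapping reported results. The rule can hide an excess or create one.

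**5. What a zero would mean.** If 0 of 180 were reported, the one-sided 95% upper limit is 1 − 0.05^(1/180) = 1.65%. With the planned 20% dropout, 180 × 0.8 = 144 patients remain, and the limit is 1 − 0.05^(1/144) = 2.06%. Either limit applies to withdrawals called related. Neither says anything about distress without withdrawal, or about an excess over control.

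**6. What recording both arms would give.** At 180 per arm and a two-sided 5% level, power to detect 2% against 6% is 49%, 5% against 10% is 44%, and 5% against 15% is 89% (assumed rates, normal approximation). A by-arm table would be fair and descriptive. It would be a sensitive test only for large differences.

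**The case against.** The strongest reply is that this is a condensed article. The Endpoints sentence says that certain withdrawals will be reported; it does not say that nothing else will be. Adverse-event definitions and withdrawal forms commonly sit in the full protocol, which is not shown. This stands as a caution: that nothing else is collected is an inference. It does not remove the point, because the article does state a rule, and that rule yields a count that cannot be compared.

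A second reply is that harm would appear elsewhere, and much of this also stands. The sample size rests on two-sided tests, and one secondary hypothesis has no direction: "Changes in symptoms and depression from baseline (T1) to 3 months (T5) will be different between the intervention and control groups". A distressed patient who stays in still contributes symptom and depression scores. Because the primary analysis uses completers, the investigators must know who completed in each arm, so unequal dropout would be visible even if its reasons were not. What remains uncovered is anxiety, the reasons for withdrawal, and a minority who worsen behind an unchanged mean.

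A reader might infer three stronger things that the article does not support:

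- **That the trial can say nothing about safety.** Survival, symptoms, quality of life and depression are all compared between arms.
- **That the control count is zero by definition.** Controls share the monitoring component.
- **That patients withdrawn for deterioration are kept out of the adverse-event count.** Study procedures does not say how such withdrawals are classified, nor that one cannot also be recorded as an adverse event.

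Finally, safety is not among the stated aims or hypotheses, and this is nurse-led counselling and education. That bears on the grade of the point, not on whether the rule is sound.

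**Conclusion.** The point holds in limited form. The stated adverse-event count is restricted to withdrawals judged related to the intervention, under open attribution and with almost no possibility of a control count. It is not comparable between arms, it misses harm without withdrawal, and it cannot support an adverse-event comparison. HADS anxiety is scored but has no planned between-arm comparison.

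The size cannot be fixed from the document. On the assumed rates, the reported difference could be anywhere from 0 to 5 percentage points when the true difference is 3, and equally when it is none. The conclusion assumes that the full protocol adds no wider recording rule; if it does, the article's sentence needs only to be brought into line with it. This is a minor, cheap improvement, and it does not touch the primary analysis.

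**What to change.** Replace the last sentence of Endpoints with:

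*In both arms, every withdrawal will be recorded with date and reason regardless of judged relatedness, with relatedness to study procedures recorded as an additional item, and counts will be reported by arm.*

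Referring to study procedures, and not to the intervention, makes the relatedness item answerable for controls too.

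Add one by-arm table of patients whose HADS anxiety or depression score worsens from baseline, with the number assessed at each visit, since withdrawn patients will be missing from it. Fix the definition of worsening before outcomes are compared. Both arms use the same monitoring system, so on the article's description the scores are already collected.

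The cost is a reason field on the withdrawal form and one table. Many withdrawals due to disease or chemotherapy will be listed in both arms, which the by-arm layout absorbs. Recruitment has already begun (Trial status), so reasons for earlier withdrawals would have to come from existing study records. A listing of every adverse event in patients on chemotherapy is a debatable burden and is not needed for this point. Deaths by arm already come from the survival endpoint.

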### Sample size determination

Advanced cancer patients (*n*=360) and their family caregivers (*n*=360) will participate in the study. Sample size was estimated based on two-sided tests with α=.05, power=.80 (=.93 x .93 x .93) considering three primary endpoints [50], and medium effect size (beta >.30) for supportive care interventions for symptoms [51], coping (.50~.55) [46], and QoL (.50) [52]. The estimated sample size for t-tests was 192, that for correlation analysis was 126, and that for multiple regression with 10 control variables was 160.

Considering structural equation modeling to analyze relationships among the studied variables, a sample size of > 300 is recommended [53]. Considering longitudinal data collection and a dropout rate of 20%, a total of 360 advanced cancer patients and 360 family caregivers will be enrolled in the study.

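### The 20% drop-out allowance is applied the wrong way round: 360 enrolled leaves 288, short of the >300 recommended for structural equation modelling; the primary t-tests are unaffected

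*Protocol article*

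**What the plan says.** Under Sample size determination, the protocol article gives four sizes for four kinds of analysis. Three are calculated: "The estimated sample size for t-tests was 192, that for correlation analysis was 126, and that for multiple regression with 10 control variables was 160". The calculation uses "two-sided tests with α=.05, power=.80 (=.93 x .93 x .93) considering three primary endpoints". The fourth is a rule of thumb from a cited source: "Considering structural equation modeling to analyze relationships among the studied variables, a sample size of > 300 is recommended". The next sentence turns this into the enrolment figure: "Considering longitudinal data collection and a dropout rate of 20%, a total of 360 advanced cancer patients and 360 family caregivers will be enrolled". No other base and no inflation formula is given.

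Structural equation modelling appears once more, under Statistical analyses, as part of the last item listed for the secondary endpoints. There it serves to describe how symptoms, depression, coping, self-efficacy and quality of life relate to each other. Neither the primary nor the secondary hypothesis rests on it.

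**The concern.** A drop-out allowance should leave the target number of patients after the losses have occurred. Here the target, the loss rate and the enrolled number stand in consecutive sentences and do not fit together: taking 20% from 360 gives fewer than 300. The figure looks like the common slip of adding the drop-out percentage to the target instead of dividing the target by the proportion retained.

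The structural equation figure is the only one of the four that explains enrolling as many as 360. A reader will therefore take it that 20% attrition is covered for the analysis that set the size, and it is not. At stake is the accuracy of the sample size statement and the support claimed for one secondary analysis.

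**Working it through.** **Inputs**, all from Sample size determination unless noted:
- target for structural equation modelling: more than 300, taken as 300 (or 301 if read strictly);
- drop-out: 20%, so 0.80 retained;
- enrolled patients: 360, allocated 1:1 (Randomization and blinding);
- t-tests: two-sided 0.05, power 0.93 per endpoint, total 192.

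**Step 1. Reproduce 360.** Each stated size is inflated both ways:

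| Base | Base / 0.80 | Base x 1.20 |
|---|---|---|
| 192 (t-tests) | 240 | 231 |
| 126 (correlation) | 158 | 152 |
| 160 (regression) | 200 | 192 |
| 300 (structural equation modelling) | 375 | **360** |

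Only 300 x 1.20 gives 360. (Fractions are rounded up.)

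**Step 2. What 360 leaves.** 360 x (1 - 0.20) = 288, and 300 - 288 = 12, a shortfall of 12/300 = 4%.

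**Step 3. Enrolment that would leave the target.** n = target / (1 - drop-out): 300/0.80 = 375; 301/0.80 = 376.25, rounded up to 377.

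**Step 4. Drop-out that 360 can bear.** 1 - 300/360 = 16.7% (1 - 301/360 = 16.4% for strictly more than 300). Both are below the stated 20%.

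**Step 5. Primary comparison.** The stated 192 reproduces: a two-sample t-test at a standardised difference of 0.50, two-sided 0.05 and power 0.93 needs 95.4 per arm, so 96 per arm and 192 in total. The joint power also reproduces: 0.93 x 0.93 x 0.93 = 0.804. With 288 completers there are 144 per arm, and power at 0.50 is 98.8% per endpoint. By the plan's own product rule, joint power is 0.988 x 0.988 x 0.988, or about 96%. Allowing for 20% drop-out, the t-tests would need 192/0.80 = 240 enrolled, well below 360.

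**The case against.** The arithmetic is hard to dispute. The case on the other side is about what it means.

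*The figure is a recommendation.* The text says "a sample size of > 300 is recommended", citing a general source; it is not a power calculation. This stands. It would be wrong to say that the trial needs 300 completers, and 288 exceeds all three calculated sizes.

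*The 288 may not be the modelling sample.* Completers are specified as the analysis set only for the primary endpoints. No time point or analysis set is given for the structural equation models, so a model using baseline or all available data could include up to 360 patients. This stands in part: the analysis set is not stated. But if the recommendation were meant for enrolled patients, the drop-out sentence that follows it would have no function, because enrolling just over 300 would already do.

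*A stronger reading a reader might infer: the symptom endpoint is underpowered.* The symptom effect is given as a beta above .30, while the other two primary endpoints have effects of about .50. Someone might read .30 as a standardised mean difference and conclude that the joint power of .80 fails. The document's own figures point away from this. The stated 126 for correlation reproduces with r = .30 at power .93, so .30 fits the correlation scale. The stated 192 reproduces with a difference of 0.50, so .30 was evidently not used for the t-tests. The text also calls the effect medium and gives .30 as a lower bound. What remains is a detail of scale that the article does not spell out, which is not an error.

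**Conclusion.** The drop-out allowance is wrong as written. At the stated 20%, 360 enrolled leaves 288 completers, 12 fewer than 300; 375 would be needed, or 377 for strictly more than 300. The arithmetic is certain. That the recommended size refers to patients remaining after drop-out is an inference from the order of the sentences, and it is the only reading that gives the allowance a purpose.

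The severity is minor. The shortfall is 4% against a rule of thumb, for a secondary analysis that no stated hypothesis depends on. It would be a mistake to infer that the trial is too small for its primary aim: on the plan's own assumption of a 0.50 difference, 144 completers per arm exceed the 96 required by half. Nothing here calls for more patients or a change of design.

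**What to change.** Keep 360 and correct the text. Under Sample size determination, state that with 20% drop-out 288 completers are expected, which is above the 192 needed for the t-tests but below the >300 recommended for structural equation modelling.

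Under Statistical analyses, state that the structural equation models will be fitted by full-information maximum likelihood on all randomised patients, using Mplus, which is already listed. Add that the >300 is then met only by counting patients with incomplete follow-up, and that the method assumes data are missing at random. That assumption deserves a sentence, because Study procedures has patients withdrawn when their condition deteriorates.

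The cost is a few sentences. Recruitment began in March 2021, and neither enrolment nor the primary analysis changes. The sample size statement becomes slightly less favourable, and correct.
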